## Abstract

**Background:**

Posterior tibial nerve stimulation (PTNS) is a promising treatment for lower urinary tract symptoms (LUTS) in patients with MS. However, long term data focusing on PTNS impact on health-related quality of life (HRQOL), bowel and bladder symptoms are lacking. This paper describes a study protocol that examines the extended efficacy of PTNS on MS related bladder and bowel symptoms and resulting HRQOL.

**Methods/Design:**

This is a single-centered, prospective, longitudinal, observational cohort study of patients with MS who suffer from LUTS and are refractory to two prior treatment modalities. Participants who have elected to pursue PTNS therapy for LUTS will be eligible. The primary outcome is the median number of urinary frequency and incontinence episodes on a 3-day voiding diary at 3, 12 and 24 months compared to baseline. Secondary outcome measures will include change in total AUA-SS, M-ISI, NBSS, SF-12, SSS and BCS scores from baseline The Expanded Disability Status Scale and magnetic resonance imaging will be evaluated at baseline and annually throughout the study.

**Discussion:**

This research protocol aims to expand on the existing literature regarding outcomes of PTNS in MS. Specifically, it will provide long term follow-up data on bladder, bowel, sexual and HRQOL outcomes. The completion of this study will provide longitudinal efficacy data of the impact of PTNS in MS patients.

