Zecca [7]	‘14	83	refractory LUTS, UDS with Dom UAB or DSD	3	• Sensory response: 64%, Motor response: 6%, Sensory-Motor: 30%; Sensory response with or without motor response was associated with better outcome than motor alone (p < 0.001)
Canbaz- Kabay [23]	‘17	initial: 29 Maint: 21	refractory OAB	12	• Improvement in frequency, nocturia, urgency (all p < 0.001) and voided volume improved mean 72 cc (p < 0.05). • Change from baseline on the ICIQ-SF, OABv8 and OAB-q: decreased symptom severity and health related quality of life (*P* < 0.001)

*all studies included adults with multiple sclerosis

**Study of Transcutaneous PTNS versus others, which were percutaneous

*UDS* urodynamics, *DO* detrusor overactivity, *MCC* Maximum Cystometric Capacity, *LUTS* Lower urinary tract symptoms, *Maint* Maintenance, *NR* Not reported

Despite these findings, the studies were limited by their short term follow up (range 3–12 months), strict inclusion criteria, and lack of important quality of life outcomes. Outcomes beyond 12 months and the impact of standard maintenance therapy have only been studied in one prior study [20]. Moreover, there is limited research on the effects of PTNS on related pelvic organ dysfunction such as bowel and sexual function among patients with MS. [23, 24] As PTNS requires significant investment on the part of patients and clinicians, further studies generating more robust evidence regarding the long term impact of this therapy are warranted. Furthermore, we believe it is important to follow PTNS treatment outcomes longitudinally to determine if it is effective in a progressive disease such as MS. Previous published PTNS studies did not address how efficacy could be affected by the type of MS, disability status or whether the efficacy could be maintained long term in the setting of a progressive disease.

Therefore, the aim of this study is to describe short- and long-term clinical outcomes, including quality of life, bladder, bowel and sexual function, in MS patients who undergo PTNS treatment for refractory LUTS.

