## Methods/Design

### Study design and population

The study is registered with clinicaltrials.gov, NCT04063852. This study is designed as a single-centered, prospective, longitudinal cohort study with plans to follow participants for up to 24 months. Adult patients at the University of Michigan outpatient urology clinic presenting with multiple sclerosis and lower urinary tract symptoms (LUTS) including urinary frequency, urgency, incontinence refractory to two prior treatments who have elected to pursue percutaneous PTNS will be invited to participate (Table 2). Refractory symptoms are defined as bothersome LUTS that have not responded to at least two prior therapies including behavior modification, pharmacotherapy, pelvic floor physical therapy or bladder onabotulinum toxin. Full inclusion and exclusion criteria are listed in Table 2.

**Table 2 Tab2:** Inclusion and Exclusion criteria

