### Sample size

In this descriptive study, we aim to enroll at least 50 participants. While it is likely that the count of episodes in each of the time frames follows a Poisson distribution, the difference statistic could very well be expected to follow a normal distribution. If not, appropriate transformations would be applied to create an approximately normal distribution. Allowing for up to a 10% dropout rate, this sample size will provide a 95% chance to have a 95% confidence interval for our change statistic that is within +/− 1/3 of a standard deviation. In other words, if we have an underlying standard deviation of 3 for the difference in counts, simulation results indicate that over 95% of the time, the 95% confidence interval for the change statistic would fall within the mean +/− 1. This will provide sufficient precision for our outcomes of interest.

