## Statistical analysis

Baseline descriptive demographic data will be presented for the entire cohort. The primary outcome of median number of urinary frequency and incontinence episodes on a 3-day voiding diary at 3, 12 and 24 months will be compared to baseline for each patient using paired analysis. Secondary outcome measures including total AUA-SS, M-ISI, NBSS, SF-12, SSS and BCS scores at 3, 12 and 24 months will be compared to baseline for each patient using paired analysis. Continuous variables will be evaluated using paired t-test and categorical data will be analyzed using McNemar’s test. Paired data will be evaluated using a 2-sided paired t-test. Median values will be analyzed using a Wilcoxon signed rank test. Statistical significance will be considered with *p* < 0.05.

In order to assess for predictors of improvement of symptoms response to PTNS, planned subgroup analysis will be performed stratifying patients based on gender, EDSS score, and burden of disease on MRI. Furthermore, an interim analysis at evaluating outcomes at 3 and 12 months after PTNS is planned.

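### The Abstract and Background promise efficacy data on PTNS, but an uncontrolled cohort compared with a single baseline diary can show only change from baseline

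*Protocol article*

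**What the plan says.** Two descriptions of the study stand side by side.

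- **Efficacy.** The Abstract's Background paragraph says the protocol "examines the extended efficacy of PTNS on MS related bladder and bowel symptoms". Its Discussion paragraph says "The completion of this study will provide longitudinal efficacy data of the impact of PTNS in MS patients". The main Background section gives as a reason for longitudinal follow-up the wish to determine whether PTNS is effective in a progressive disease.
- **Description.** The Abstract's Methods/Design paragraph states: "This is a single-centered, prospective, longitudinal, observational cohort study of patients with MS who suffer from LUTS". The Background section closes by saying that "the aim of this study is to describe short- and long-term clinical outcomes". The Sample size section opens: "In this descriptive study, we aim to enroll at least 50 participants".

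All participants have elected PTNS. Table 3 and the Study measurements section schedule one diary at month 0, the time of first treatment, and further diaries at months 3, 12 and 24. Under Statistical analysis, the primary outcome at each follow-up visit "will be compared to baseline for each patient using paired analysis", with a two-sided paired t-test, or a Wilcoxon signed rank test for medians, at p < 0.05. The document describes no control or sham group, no run-in and no external comparator. It does not name the lack of a control as a limitation.

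**The concern.** A paired test against baseline has the null hypothesis of no change. An efficacy statement needs the null hypothesis of no PTNS effect. In a single-arm study these differ by whatever would have happened without active stimulation: placebo response, regression to the mean and disease course.

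The protocol gives reason to think this difference need not be zero. Under Study design and population, "Refractory symptoms are defined as bothersome LUTS that have not responded to at least two prior therapies", so patients enter when symptoms trouble them enough to seek a further line of treatment. The Background section says that relapsing-remitting patients may recover fully from a relapse and that primary progressive disease may include temporary improvement. It also describes MS as progressive, which would push symptoms the other way and could hide a benefit.

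The Discussion section wants the quality-of-life results to help clinicians and patients judge whether PTNS is worth the investment. If a fall from baseline is read as efficacy, that judgement rests on an attribution the design cannot make.

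**Working it through.** **The plan's own figure.** The protocol gives no figure for attribution. Its one calculation, under Sample size, concerns precision: 50 enrolled with up to 10% dropout are said to give a 95% chance that the 95% confidence interval lies within ±1/3 SD. Taking the criterion as half-width ≤ SD/3, the chance is P(χ² with n − 1 df ≤ (n − 1)n / (9t²)). This gives 86.0% at n = 45 and 95.8% at n = 50, so the figure fits 50 completers. That mismatch is a separate matter. Precision about a change says nothing about its cause.

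**Inputs for the illustration**
- n = 45: 50 enrolled less 10% (Sample size).
- SD of the within-patient difference = 3 episodes (Sample size, where it is itself illustrative).
- Two-sided paired t-test at 0.05 (Statistical analysis). The critical value at 44 df is about 2.015.
- PTNS effect = 0.
- Non-PTNS fall from baseline: **assumed**, since the document gives none.

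**Formula.** The noncentrality is δ = (shift / 3) × √45 = (shift / 3) × 6.708. The probability of a significant improvement is P(T > 2.015), where T is noncentral t with 44 df and noncentrality δ.

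| Assumed non-PTNS fall (episodes) | In SDs of change | δ | P(significant improvement), one test |
|---|---|---|---|
| 0 | 0 | 0 | 2.5% |
| 0.5 | 0.167 | 1.12 | 19% |
| 0.9 | 0.30 | 2.01 | 50% |
| 1.0 | 0.333 | 2.24 | 59% |
| 1.5 | 0.50 | 3.35 | 91% |
| 2.0 | 0.667 | 4.47 | 99% |

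The probability passes 50% at about 0.30 SD (0.9 episodes) and 80% at about 0.43 SD (1.28 episodes).

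**Regression to the mean alone.** This was simulated with n = 45 and an assumed baseline–follow-up correlation of 0.5 to 0.9. The result depends on how strongly entry selects on the baseline diary value:
- no selection: 2.5%;
- baseline above −1 SD of the wider population: 6% to 16%;
- above −0.5 SD: 12% to 43%;
- above the mean: 22% to 82%.

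The eligibility criteria set no diary cut-off, so the document does not say which line applies.

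**The case against.** The strongest reply is that the protocol is already open about its design. The Abstract calls it observational, the aim is to describe, and the sample size rests on interval width rather than on power for an efficacy test. The Conclusion repeats the promise as 24-month follow-up data without claiming efficacy. Patients who do not go on to maintenance are still followed, and EDSS and MRI record disease course. Limitations of uncontrolled data are often stated in the results paper. Much of this stands: a descriptive single-arm cohort is legitimate, and the problem is confined to wording. It does not remove the wording, which states a conclusion the design cannot deliver. Recording EDSS and MRI tracks disease course but supplies no comparator.

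A reader might infer more, namely that a significant improvement is *likely* even if PTNS does nothing. The document does not support this. It gives no test–retest correlation, diary threshold or placebo shift, and the table above runs from 2.5% to 99% depending on what is assumed. Regression to the mean can act only indirectly, through when patients present. Symptoms that persist through two failed therapies point to chronic disease at least as much as to a temporary peak. Progression could also bias the comparison against PTNS.

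A reader might also infer that a second pre-treatment diary is needed. A short interval before time 0 cannot estimate drift over 3 to 24 months, and it captures no placebo response to sessions that have not begun. That would be a design preference, not the repair of an error.

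**Conclusion.** The point holds as a conflict between the stated conclusion and the design. The Abstract and Background claim efficacy, while the same document sets out an uncontrolled, descriptive cohort whose paired tests detect any change from a single baseline diary. This follows from the text alone and needs no assumption.

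The size of the possible error is not known. If the non-PTNS fall were 0.5, 0.9 or 1.0 episodes, the chance of a significant improvement with no PTNS effect would be 19%, 50% or 59% per test, against 2.5% with no shift. These figures rest on 45 evaluable patients, an SD of 3 and shifts chosen for illustration. They show that modest drift can matter at this sample size, not that it will occur.

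**What to change.** 1. In the Abstract (Background and Discussion paragraphs) and in the Background section, replace the terms *efficacy*, *impact of PTNS* and *effective* with *change from baseline in patients treated with PTNS*.
2. State, for example under Statistical analysis, that a significant paired change will not be interpreted as a PTNS effect. Give the reason: the design is uncontrolled and does not separate placebo response, regression to the mean or disease course, which can act in either direction.

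The cost is a few sentences and a less favourable claim. Data collection, sample size and tests stay as they are, and neither a control arm nor an extra diary is needed for this point.

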**Trial registration:**

NCT04063852.

## Background

Multiple Sclerosis (MS) is the most common autoimmune neuro-inflammatory disease of the central nervous system and affects approximately 31 per 100,000 Americans annually, with 700,000 Americans living with MS in 2010 [1].

MS is characterized by four primary disease courses: clinically isolated syndrome (CIS), relapsing remitting (RRMS), secondary progressive (SPMS) and primary progressive (PPMS) [2, 3]. Clinically isolated syndrome is a pre-MS syndrome and is described as the initial episode of neurologic deficit which may progress to MS. [2] In some patients, CIS precedes the diagnosis of relapsing-remitting MS (RR-MS). Relapsing-remitting MS (RRMS) is characterized by discrete episodes of neurological dysfunction or relapses, with no interim disease progression. Patients may fully recover from a relapse or may experience residual deficits. Secondary progressive MS patients have gradual neurological deterioration (progression) with increasing physical debilitation following a period of relapsing remitting disease [4]. Finally, primary-progressive MS (PPMS) is defined as steady disease progression from its onset and may include periods of stable disease or temporary symptomatic improvement [5].

Lower urinary symptoms (LUTS) including overactive bladder (OAB) are reported in 75–90% of all MS patients, and can be very bothersome to patients [6]. However, stage and type of disease may impact perception and severity of urinary symptoms in MS patients. Utilizing urodynamic data, others showed that there is high prevalence of urinary symptoms even in clinically isolated syndrome (CIS), before greater neurologic impact from the disease is found [7]. Once patients have established disease, urinary symptoms may be perceived differently based on rapidity of disease progress.

Current management of MS related LUTS follows the overactive bladder pathway: first line lifestyle modifications, second line adjunctive pharmacotherapy, third line neuromodulation (sacral or posterior tibial) or chemodenervation of the bladder (onabotulinum toxin) and fourth line invasive surgical reconstruction [8–10]. The implementation of intermittent or indwelling catheter can be an adjunct to these therapies (Fig. 1).

**Fig. 1 Fig1:**
[figure not shown]
Management of Lower Urinary Tract Symptoms in Patients with Multiple Sclerosis

Each intervention can have significant quality of life implications. For example, second line pharmacotherapy with anticholinergic is often poorly tolerated because it can exacerbate symptoms of dry mouth, constipation and central nervous system side effects like confusion [8]. Likewise, the addition of intermittent catheterization can add complexity to the patient’s lifestyle with unclear impact on decreasing LUTS [11]. In regards to third line therapy, intradetrusor onabotulinumtoxin (Botox) can be effective at controlling symptoms, but it requires cystoscopy to administer, the treatment needs to be repeated every 6–12 months, and each administration carries a risk of urinary tract infection and urinary retention [12].

Neuromodulation, another third line therapy, includes both sacral neuromodulation and posterior tibial nerve stimulation. Sacral neuromodulation involves 1 or 2 surgeries for placement of a neuromodulation lead and an implantable pulse generator to stimulate the S3 nerve root. Limited data suggest sacral neuromodulation may be effective for MS related LUTS, however the sacral neuromodulation leads are not MRI compatible [8, 13, 14]. Since many patients with MS require frequent MRI for surveillance, this poses a barrier for use of current implantable sacral neuromodulation technology. In these patients, percutaneous posterior tibial nerve stimulation (PTNS) offers a minimally invasive alternative to relieve bladder symptoms via similar pathways as sacral neuromodulation.

Posterior tibial nerve stimulation, involves placement of a solid stainless-steel needle into the posterior tibial nerve and uses this to conduct a fixed electrical pulse through the nerve. The posterior tibial nerve derives from the L4-S3 nerve roots, neuromodulation of this nerve has been shown to improve overactive bladder symptoms [15]. The office-based therapy is performed weekly for 12 weeks during 30-min sessions; patients who have improvement in symptoms can proceed to maintenance treatments at regularly scheduled intervals.

Only seven clinical studies have been published regarding the use of PTNS in patients with MS and refractory LUTS [16–22]. (Table 1) Of these studies, four represent prospective case series evaluating the efficacy of PTNS for LUTS in MS, with a total of 131 patients [18–20, 22]. These studies reported significant improvement in LUTS with overall the rate of improvement (defined as greater than 50% improvement in symptoms) between 33 and 89% (Table 1).

**Table 1 Tab1:** Literature review of Posterior Tibial Nerve Stimulation in Multiple Sclerosis

Author	Year	N	Inclusion Criteria*	Follow-up (months)	Primary Outcome Results
Fjorback [1]	‘07	8	UDS: DO and MCC < 300 mL	n/a	• PTNS unable to suppress detrusor contraction. • No reduction of urgency • No difference in peak detrusor pressure • Median volume at first contraction was 36% higher with stimulation. (*p* = 0.0078)
Kabay [2]	‘08	29	storage symptoms	n/a	• Mean volume first involuntary contraction increased from 183 to 230 mL. (*p* < 0.001) • Mean maximum cystometric capacity increased from 193 to 286 mL. (*p* < 0.001)
Kabay [3]	‘09	19	LUTS	3	• Complete Response rates > 50% improvement: urgency (33%), incontinence (40%), frequency (58%), nocturia (75%), pad test (90%) of patients • Partial Response between 25 and 50% improvement:urgency (53%), incontinence (50%), frequency (26%), nocturia (25%), pad test (10%) of patients • UDS response: DSD resolved in 3/5, significant improvement after PTNS in first involuntary detrusor contraction volume, MCC, Qmax, PVR (*p* < 0.05)
de Seze [4]**	‘11	70	refractory OAB symptoms	3	• 30d: 51% resolution of severe urgency, 67% reduction in frequency by 3 episodes/day • 90d: improvement in 83.3% of patients in 3 day bladder diary, MHU or warning time
Gobbi [5]	‘11	18	refractory LUTS	3	• Improved frequency, nocturia, Increased voided volume, • PPBC decreased by 3 points (*p* = 0.003), PPIUS decreased by 2 points (*p* = 0.005), UB-VAS decreased by 4 cm (p = 0.005), improvement in KHQ (p < 0.05)
Zecca [6]	‘14	initial: 83 Maint: 74	refractory LUTS, UDS with DO, UAB or DSD	24	• 60% (44/74) required maintenance every 2 weeks, 4% required maintenance every week, mean treatment was: 1.79 sessions/patient/month • 82% of patients reported treatment satisfaction on TS-VAS, GRA, and PPBC at 24 months
Zecca [7]	‘14	83	refractory LUTS, UDS with Dom UAB or DSD	3	• Sensory response: 64%, Motor response: 6%, Sensory-Motor: 30%; Sensory response with or without motor response was associated with better outcome than motor alone (p < 0.001)
Canbaz- Kabay [23]	‘17	initial: 29 Maint: 21	refractory OAB	12	• Improvement in frequency, nocturia, urgency (all p < 0.001) and voided volume improved mean 72 cc (p < 0.05). • Change from baseline on the ICIQ-SF, OABv8 and OAB-q: decreased symptom severity and health related quality of life (*P* < 0.001)

*all studies included adults with multiple sclerosis

**Study of Transcutaneous PTNS versus others, which were percutaneous

*UDS* urodynamics, *DO* detrusor overactivity, *MCC* Maximum Cystometric Capacity, *LUTS* Lower urinary tract symptoms, *Maint* Maintenance, *NR* Not reported

Despite these findings, the studies were limited by their short term follow up (range 3–12 months), strict inclusion criteria, and lack of important quality of life outcomes. Outcomes beyond 12 months and the impact of standard maintenance therapy have only been studied in one prior study [20]. Moreover, there is limited research on the effects of PTNS on related pelvic organ dysfunction such as bowel and sexual function among patients with MS. [23, 24] As PTNS requires significant investment on the part of patients and clinicians, further studies generating more robust evidence regarding the long term impact of this therapy are warranted. Furthermore, we believe it is important to follow PTNS treatment outcomes longitudinally to determine if it is effective in a progressive disease such as MS. Previous published PTNS studies did not address how efficacy could be affected by the type of MS, disability status or whether the efficacy could be maintained long term in the setting of a progressive disease.

Therefore, the aim of this study is to describe short- and long-term clinical outcomes, including quality of life, bladder, bowel and sexual function, in MS patients who undergo PTNS treatment for refractory LUTS.

## Methods/Design

### Study design and population

The study is registered with clinicaltrials.gov, NCT04063852. This study is designed as a single-centered, prospective, longitudinal cohort study with plans to follow participants for up to 24 months. Adult patients at the University of Michigan outpatient urology clinic presenting with multiple sclerosis and lower urinary tract symptoms (LUTS) including urinary frequency, urgency, incontinence refractory to two prior treatments who have elected to pursue percutaneous PTNS will be invited to participate (Table 2). Refractory symptoms are defined as bothersome LUTS that have not responded to at least two prior therapies including behavior modification, pharmacotherapy, pelvic floor physical therapy or bladder onabotulinum toxin. Full inclusion and exclusion criteria are listed in Table 2.

**Table 2 Tab2:** Inclusion and Exclusion criteria

